#### Recruitment

Each month, proportions of stroke patients meeting the inclusion criteria for the trial and proportions of these patients actually recruited will be presented and compared between clusters and between intervention groups, both descriptively and inferentially using chi-square tests. Every three months we will also investigate descriptively whether there is an association between a cluster's reported eligibility rate and the percentage of recruited patients with mild incontinence using a range of appropriate techniques, including graphical representation and rank correlations.

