### Patient recruitment process

Patients who meet the inclusion criteria will be approached as early as possible following admission to the participating stroke unit. Patients who do not meet the inclusion criteria early post-stroke will be approached as soon as possible if they subsequently meet the inclusion criteria. Nursing staff will ask each eligible patient whether his/her name can be given to the research team. If the patient agrees, a member of the research team will visit the patient, explain the project, answer any questions they may have and provide an information leaflet. Patients will be given at least 24 hours to consider participation and will be visited by a member of the research team after this period; patients choosing to participate will sign the consent form at this stage.

For patients unable to consent for themselves, a person able to advise on the presumed wishes of the patient will be approached to act in the role of consultee. This is in line with the recommendations of the Mental Capacity Act [38] and in line with the expressed wishes of the study Patient, Public and Carer Involvement groups, who would like everyone who is eligible to have the opportunity to participate.

Recruitment rates in each cluster will be monitored on a monthly basis to identify both quantitative (i.e. numbers of participants recruited) and qualitative (i.e. patient characteristics) imbalance across clusters [39]. Should identified imbalance be indicative of likely selection bias (e.g. cluster with low proportion of stroke patients identified as eligible but high proportion of those eligible with severe incontinence), we will review the recruitment process and address any issues identified.

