### Sample Size

The sample size is chosen pragmatically, rather than on the basis of a formal power calculation; our aim is to balance practicalities and the need for reasonable precision in the estimation of effects to inform the sample size calculation for a full-scale trial to test effectiveness.

The use of four stroke services per arm (12 in total) will provide a satisfactory indication of likely effectiveness and help us address any feasibility issues relating to the delivery of the interventions. It will also provide some degree of confirmation regarding the size of the intra-class correlation coefficient and will enable us to perform a review of the number of sites (and the number of patients needed per site) for each arm of the trial for a full-scale trial. It will also provide some information on stroke service-level factors which may help explain the variability in outcome between stroke services in each arm, thus helping reduce the intra-class correlation coefficient and hence achieve efficiency in terms of the number of stroke services required for a full-scale trial.

Twelve stroke services will admit around 4800 patients per year, of whom we expect around 20% will meet the trial inclusion criteria and consent to participate. To achieve better balance in the number of participants recruited per Trust, we will recruit for 12 months in services which admit 300 or less patients per year and for 9 months in Trusts which admit more than 300 patients per year; we expect that this will enable us to recruit 780 patients across the 12 services.

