#### Outcomes

The primary analysis set will be defined as the intention-to-treat population. All stroke services randomised will be retained in the trial. Outcome data will be collected from all consented patients whenever possible, whatever their level of subsequent engagement with the allocated intervention programme. If there is more than 10% loss to follow-up overall or moderately differential loss to follow-up across stroke services, a secondary per-protocol analysis will also be considered. The decision as to whether a per-protocol analysis will be informative will be made by the trial statistician in conjunction with other members of the Trial Management Group; this decision will be made without reference to the recorded values of the outcome data.

To account for the cluster randomisation, we shall use mixed effects modelling for continuous, ordinal and dichotomous outcomes to compare the two groups on primary and secondary outcome data. Baseline measures of the outcomes variables (where appropriate), stroke classification, type of incontinence and the other prognostic patient-level information (from the Edinburgh case-mix adjuster) will be included as individual-level covariates in the models for outcome data.

Missing outcome data will be imputed according to the particular outcome. For the primary analysis, dichotomous and ordinal outcomes for those who withdraw, die or are otherwise lost to follow-up will be imputed using a worst-case scenario (e.g. for the primary outcome variable, all those for whom incontinence status is not recorded at 6-weeks post-stroke will be assumed to be incontinent). For continuous outcomes, the primary analysis will use a non-parametric multiple imputation approach [66].

The effect of stroke service-level factors will also be explored in the modelling; this will enable appropriate stratification to be used in the future larger scale trial, if desired, and to potentially reduce the size of the intra-stroke service correlation coefficient by reducing the unexplained component of the variability between stroke services. This analysis will be used to confirm the sample size necessary for the future trial and to provide estimates (including 95% confidence intervals) of the effectiveness of each intervention relative to usual care.

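### The between-arm chi-square tests on eligibility and recruitment treat patients as independent although whole services were randomised, so they are anti-conservative to a degree that depends on an unstated ICC

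*Protocol article*

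**What the plan says.** In the protocol article, Data analysis, the Recruitment section names two proportions to be examined: "Each month, proportions of stroke patients meeting the inclusion criteria for the trial and proportions of these patients actually recruited". It states that these will be presented and "compared between clusters and between intervention groups, both descriptively and inferentially using chi-square tests". It names no cluster adjustment, significance level or rule for repeated testing, and it does not say whether each look uses that month's data or all data so far. The same section adds a three-monthly descriptive check relating a service's eligibility rate to its share of mild cases.

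The Sequence generation section randomises services, one to each arm within each of four strata. The Outcomes section under Data analysis deals with clustering for outcome data: "To account for the cluster randomisation, we shall use mixed effects modelling". No matching statement is made for the recruitment comparisons.

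The Patient recruitment process section says what the monitoring is for: "Should identified imbalance be indicative of likely selection bias", the team will review recruitment and deal with whatever is found.

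**The concern.** A Pearson chi-square between arms is valid if every admission is an independent draw from its arm's common rate. Here the rate belongs to the service, and an arm is only four services. If services differ at all in case mix, screening practice or consent rates, the arm proportions will differ by more than binomial error, even with no effect of allocation. The test reads that excess as a difference between arms.

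The article itself expects services to differ: it compares them with each other, monitors imbalance across them and stratifies on their characteristics.

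The between-arm comparison matters because the Allocation concealment section says that recruiting staff will know their service's allocation. A reader would therefore take an arm difference in eligibility or recruitment as a sign of selection bias. A test that flags ordinary service variation too often is a poor guide to that, both during the trial and when recruitment balance is reported.

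**Working it through.** **The plan's own figures.** The article states no alpha, ICC or false-alarm rate for these tests, so there is no figure to reproduce directly. The nearest computed number is the target of 780. From the Sample Size section, 0.20 × 4800 = 960 if all services recruit for 12 months, and 0.75 × 960 = 720 if all recruit for 9. A total of 780 requires (780 − 720)/(0.20 × 0.25) = 1200 admissions a year in the smaller services. That is feasible, but the split is not stated. The admission figure is used below as given.

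**Inputs from the article**
- Three arms of four services each, so the between-arm test has 2 df.
- "Twelve stroke services will admit around 4800 patients per year": 4800/(12 × 12) ≈ 33.3 per service per month, or 300 per service over nine months.
- "we expect around 20% will meet the trial inclusion criteria and consent to participate".
- Nine to twelve monthly looks, from the 9- and 12-month recruitment periods.

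**Assumptions**
- ICC from 0.001 to 0.05.
- Equal service volumes, service rates that persist over time, and no arm effect.
- For recruitment: 40% of admissions eligible (about 13 per service per month) and half of those recruited, which agrees with the article's 20% because 0.40 × 0.50 = 0.20.

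To give the ICC a scale, the SD of service rates is √(p(1−p) × ICC). At p = 0.40 this is √(0.24 × 0.01) ≈ 0.05 at ICC 0.01 and √(0.24 × 0.05) ≈ 0.11 at ICC 0.05.

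**Formula.** Design effect DEFF = 1 + (m − 1) × ICC. The 2-df statistic is inflated by about DEFF, so the actual size at nominal 5% is P(χ²₂ > 5.99/DEFF) = exp(−5.99/(2 × DEFF)).

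**Eligibility, between arms**

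| ICC | DEFF, one month (m = 33.3) | Size | DEFF, nine months cumulated (m = 300) | Size |
|---|---|---|---|---|
| 0.001 | 1.03 | 5.5% | 1.30 | 10% |
| 0.005 | 1.16 | 7.6% | 2.50 | 30% |
| 0.01 | 1.32 | 10% | 3.99 | 47% |
| 0.02 | 1.65 | 16% | 6.98 | 65% |
| 0.05 | 2.62 | 32% | 15.95 | 83% |

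A beta-binomial simulation (20,000 runs) agrees with these to within about one percentage point, and it gives nearly the same result for an eligibility rate of 20% or 40%.

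**Recruitment among eligible patients (simulated).** One month: 6.6% at ICC 0.01, 9.3% at 0.02 and 16% at 0.05. Cumulated to nine months: 25%, 40% and 65%.

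**Repeated looks, kept separate.** With nine separate monthly tests of one proportion and no clustering at all, the chance of at least one false alarm is 1 − 0.95⁹ = 37%. With clustering, the simulated chance for eligibility rises to about 59% at ICC 0.01 and 83% at 0.05. Only the part above 37% is due to clustering.

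**Check of a remedy.** A one-way F test on the 12 service proportions (2 and 9 df) has a simulated single-look size of 4.8% to 5.3% for ICCs of 0.01 to 0.10. It does not remove the excess from repeated looks.

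**The case against.** Four arguments count against giving this much weight.

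1. **The size depends on an assumption.** A reader might infer that false alarms run at several times 5%. The documents do not support that as a fact, because they give no ICC for either proportion. On one month's eligibility data the inflation is about twofold or less at ICC 0.01 and below. For recruitment among eligible patients it reaches about threefold only near ICC 0.05. The nine-month figures apply only if data are cumulated, which the article does not say. Allocating one service per arm within each stratum removes some between-service variance from the arm comparison, so all the figures lean high for a given total ICC. This objection stands and limits the claim.

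2. **No p-value leads to action.** A reader might infer that a significant arm difference would cause recruitment to be changed. The Patient recruitment process section acts on a judgement of likely selection bias. Its example is a pattern of eligibility and severity within a service, and the response is a review. This stands.

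3. **The trial's estimates are untouched.** The first objective concerns recruitment and retention rates, which are presented descriptively. Nothing in the outcome models or effect estimates uses these tests. This stands.

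4. **A sensitive screen can be defended**, since recruiters know the allocation and a false alarm costs only a review. This stands in part. An over-sensitive screen is acceptable if it is labelled as one, but the article presents the test as inferential, and a p-value that ignores the unit of randomisation does not have its stated meaning.

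None of these removes the error. The test is named in the text, so this is not a detail left to an analysis plan.

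**Conclusion.** The concern holds in a limited form. The between-arm chi-square uses the wrong unit of analysis and is anti-conservative whenever services vary. Under assumed ICCs of 0.001 to 0.05, its actual size on one month's eligibility data is about 5.5% to 32%, and about 10% to 83% on nine cumulated months. It is lower for recruitment among eligible patients. These values rest on equal service volumes and ignore stratification, and the excess from repeated monthly looks comes on top. The between-cluster chi-square is not affected, because there the service is itself the group being compared.

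The importance is moderate to minor. What is at risk is the reading of recruitment monitoring and of any reported p-value for recruitment balance between arms. The effectiveness analysis is not at risk.

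**What to change.** In the Recruitment section, replace the between-arm chi-square with one of the following:
- a service-level test on the 12 service proportions, such as a permutation test within the four strata or an analysis of variance with service as the unit. With one service per arm in each stratum there are (3!)⁴ = 1,296 possible allocations;
- a cluster-adjusted test;
- a descriptive comparison of arms with no p-value.

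The between-cluster chi-square may stay. The text should also say whether each look uses that month's data or cumulative data, and that repeated p-values are not corrected for the number of looks, since a service-level test does not solve that. Testing less often would reduce that excess but is a matter of preference.

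The cost is a change of wording and little programming. The drawback is that a valid test on 12 services is less sensitive to real imbalance, so the descriptive displays by service, including the three-monthly check already planned, would carry more of the weight.

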#### Intervention fidelity data

For the intervention groups, fidelity measures will be summarised using mean (with standard deviation) or median (inter-quartile range), depending on the distributions of the percentage fidelity measures. Fidelity will be compared across intervention groups and across different conservative interventions (i.e. bladder training, prompted voiding and pelvic floor muscle training).

#### Qualitative data

Qualitative interviews will be audio taped, transcribed and subject to thematic analysis using FRAMEWORK [67] to identify emergent themes. FRAMEWORK method permits identification and cross-classification of variables from paper transcriptions. The analysis process consists of identifying key concepts and mapping their range and diversity, followed by a process of interpretation where patterns of association are investigated and possible reasons for these explored. The validity of the interpretation will be assessed through regular discussion by the project team.

### Economic evaluation

In this pilot trial, we will develop data collection tools to record resource use which will be used in a future, definitive trial. Tools will include: proformas for staff to record training and time spent on the intervention; a structured staff-observation schedule to allow independent assessment of time spent on the intervention; proforma to record resources (e.g. tests and investigations, length of stay) used in hospital (data will be obtained from the hospital information system); postal questionnaire about health and social service input, for self-completion by patients and carers. The postal questionnaires will be based on a design used previously by the applicants when querying input after discharge in a cohort of stroke patients.

Two measures will be used for the cost-utility analysis. The EuroQol (EQ-5D)[55], a generic quality of life measure, will be used to facilitate comparison with other studies and will allow us to estimate the benefit of the intervention in terms of quality adjusted life years (QALYs) gained. However, it has been suggested that the EQ-5D has a large ceiling effect and poor responsiveness in a non-stroke sample of women with urinary incontinence [68]. We will therefore also use a condition-specific measure, the Incontinence-Specific Quality of Life instrument (I-QOL, [52,53]), which has been shown to be the best continence-specific measure for use in clinical trials in terms of reliability, validity and responsiveness to change [67].

We will build on the cost-utility analysis by conducting an additional sensitivity analysis. We will review published economic evaluations that have estimated Quality Adjusted Life Years (QALYs) and extract the utility (quality-of-life) values they used. We will tabulate the basis for these figures in terms of the size of sample, which patients were questioned, what technique was used (EQ-5D or other), and how values were derived. We will use the data which seem to have the most validity in the sensitivity analysis.

### Ethical aspects

The trial has been approved by Bradford Research Ethics Committee (Reference number 10/H1302/60), which has a lead responsibility for studies with Mental Capacity issues, and by local Research and Development departments.

Informed consent to participate in the trial will be sought from participants themselves or from a consultee, as outlined above. All patients will be informed that participation is voluntary and that they are able to withdraw at any time. Urinary incontinence is a sensitive issue and we believe the approach taken with participants needs to reflect this. Our study has two dedicated Patient, Public and Carer Involvement groups, and these have provided advice on recruitment strategies as well as assisting in the development of patient documentation.

### Trial management and monitoring

The Management Group (comprising all programme applicants) meets every 3 months to discuss the day to day management and running of the programme. The Trial Steering Committee meets every 6 months with a remit including review of objectives and progress against plans and objectives and monitoring the quality of the research to help ensure it contributes to knowledge at a national and international level.

The Data Monitoring Committee (DMC) will be responsible for safeguarding the interests of trial participants, assessing the effect of the interventions during the trial, and for monitoring the overall conduct of the clinical trial. The DMC will be advisory to the Trial sponsor and the Trial Steering Group and will meet biannually.

## Abbreviations

ADLs: Activities of daily living; DMC: Data Monitoring Committee; EQ-5D: EuroQol quality of life measure; ICIQ-SF: International Consultation on Incontinence Questionnaire - Short Form; ICONS: Identifying Continence OptioNs after Stroke study I-QOL: Incontinence Quality of Life instrument; MRC: Medical Research Council; NHS: National Health Service; NIHR: National Institute for Health Research; OCSP: Oxford Community Stroke Project; PPC Groups: Patient, Public and Carer Involvement Groups; QALYS: Quality Adjusted Life Years; SRN: Stroke Research Network; UI: Urinary incontinence; UK: United Kingdom; WHO: World Health Organization
